#### Ensuring indicator quality

Each indicator must meet multiple criteria regarding its validity, comprehensiveness, impact, feasibility, and usability (see Additional file 1). An indicator information form will be used to ensure the criteria are addressed and document all relevant information for each indicator (see Additional file 2). The resulting indicators will be used as the measures needed to assess change in care coordination (i.e., phase 3).

#### Advisory team review

Once indicators are drafted, the objectives and indicators will be presented to the advisory team for review and feedback. This step is essential for checking accuracy and completeness of the system, ensuring alignment with leadership objectives, and securing buy-in from outside the design team. To accomplish this, the incumbent design team members (not the facilitator, though he/she will be in attendance) will present the objectives and indicators to the advisory team in a 1-h meeting.

### Step 3: prioritize indicators by developing contingencies

In the ProMES methodology, contingencies refer to what *level* of performance is acceptable or how much a given level of improvement is valued. Contingencies are represented graphically as a function that shows how much a given performance level on a given indicator contribute to overall effectiveness (in this case PACT coordination effectiveness; see Fig. 2). A contingency function is generated for each indicator. By relating each indicator to overall coordination effectiveness, they are put on the same measuring scale, ranging from −100 to +100. Thus, the various indicators can be directly compared, prioritized, and combined into a single measure. Most importantly, it reflects an explicit statement of relative priority among the different elements of coordination and defines levels of coordination-related performance that are expected and valued by the PACT and the facility.

**Fig. 2 Fig2:**
[figure not shown]
Sample contingency graph. Note: This graph is used to help translating the score of the indicator to effectiveness on the overall coordination. Zero on the vertical axis represents the expected level of the indicator. One hundred on the vertical axis represents the maximum level of the most important indicator. Minus 100 represents the minimum level of the No. 1 minimum indicator if performing poorly on this indicator effect overall coordination as much as the most important indicator. Then assign max scores to each indicator relatively to the most important indicator and the min scores to each indicator relatively to the No. 1 minimum indicator

#### Creating contingencies

The design team will convene for a total of 6–8 h to develop a contingency function for each indicator. The design team must identify the maximum and minimum possible levels of performance, the minimum expected performance level, and scale the various levels of performance to a common metric of effectiveness for each indicator. Pritchard and colleagues explain this protocol in detail [23].

#### Leadership approval and implementation planning

Once the list of contingencies has been completed to the satisfaction of the group, the incumbent design team members (not the facilitator, though he/she will be in attendance) will present them in a 1–2 h meeting with senior leadership to obtain formal approval of the contingencies.

### Data analysis

No data analysis will occur during developmental phase 1.

## Phase 2: identify the specific information needed at the point of care to improve coordination and recommend point-of-care aids for delivering the needed information

### Design

For this aim, the design and advisory teams will participate in structured meetings in a format similar to ProMES to identify point-of-care coordination information needs. In addition, using the measures created in phase 1, we will begin collecting baseline coordination data at the sites intended to be studied in phase 3.

### Participants

The participants for this aim will be the members of the design and advisory teams described in phase 1.

### Procedures

#### Begin measuring coordination

Upon completion of phase 1, we will begin securing the necessary permissions to obtain the data required for generating the indicators developed during phase 1. Subsequently, measurement of PACT coordination will begin at all four sites, using the measures developed in that aim. The period between completion of phase 1 and identification of point-of-care aids will serve as a baseline; during this period, we will provide no feedback, only passively monitor coordination.

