### Project description and study design

This project consists of three phases: (1) developing measurable, prioritized point-of-care criteria for effective PACT coordination, to be accomplished using ProMES (detailed below); (2) identifying the specific information needed at the point of care to improve coordination and recommend point-of-care aids for delivering the needed information, to be accomplished via focus groups with the phase 1 participants; and (3) assessing the effect of adopting the aforementioned coordination standards and point-of-care aids on PACT clinicians’ coordination behaviors.

Phase 3 consists of a trial with two arms: (1) a concurrent control arm drawn randomly from PACTs which will be monitored passively and (2) a measurement and feedback arm (two sites from a single regional network), which will be involved in designing the coordination measures and identifying the point-of-care aids and will receive periodic feedback on their coordination performance. The design of the three phases of the study is summarized in the flow chart in Fig. 1. Each phase is discussed below in detail.

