## Phase 1: develop measurable, prioritized point-of-care criteria for effective PACT coordination

### Overview of ProMES methodology

A common way to help develop new tools and products such as the point-of-care aids, we propose to identify in phase 2, is the use of focus groups to identify user needs [3, 22]. One drawback of the traditional focus group approach, however, is that it can easily result in haphazard and unsystematic identification of barriers, facilitators, and solutions, particularly in the hands of an inexperienced facilitator. With a complex topic such as coordination, unsystematic responses are even more likely. The complexities of this topic demand a structured, systematic process to walk users logically and comprehensively through all of the relevant components of coordination. Once PACT members have a clear picture of the criteria for successful coordination, identifying coordination information needs will be more feasible. Thus, developing measures and criteria for effective coordination not only teaches PACT members what effective coordination should look like but also will help identify coordination information requirements in patient care. To accomplish this aim, we will use ProMES [20, 23] as the primary method of data collection and identification of point-of-care information needs.

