ProMES is a comprehensive productivity improvement approach firmly grounded in motivational theory [24, 25] and performance measurement. It utilizes diagnostic measurement to optimize the effectiveness and performance of people in complex organizations. ProMES is designed with implementation in mind: incumbents of a given work unit, supervisors, and upper level management will engage in the development of measures for capturing each important aspect of their daily work (in this case coordination). Through a facilitated process, these measures are defined, weighted, and prioritized in order to create indicators of both overall effectiveness and specific aspects of daily work. Moreover, ProMES helps address all three of Okhuysen and Bechky’s integrating conditions of coordination. The process of identifying objectives helps clarify expectations (plans and rules), which helps improve shared understanding among PACT members; the process of developing indicators and contingencies helps clarify roles and routines (thereby improving predictability and accountability) by making expectations clear, thus requiring team members to think about what they need to perform to standard.

Previous research in intensive care unit and mental health care settings has shown that successful use of ProMES can improve efficiency and quality of care. For example, in studies conducted with a German mental health hospital the ProMES methodology was utilized across organizational levels for the top management team, samples of nurses, and three samples of technicians. Results indicated that overall productivity scores for participating units were, on average, 0.78 standard deviations higher after implementation [23].

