### Procedures

#### Begin measuring coordination

Assessment of change requires a baseline; consequently, we will use the time period between completion of phase 1 and completion of phase 2 to passively monitor coordination at all study sites.

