### Trial status

Phase 1 of this study, measure development, is nearly complete. Both design and advisory teams were formed to develop and evaluate the objectives, indicators, and contingencies. These development meetings are complete; we are now finalizing the specific data sources for the indicators developed, which will be used to prepare the feedback reports in phase 3. The core study team is currently in phase 2 of the study and preparing for phase 3. We have modified our control arm sampling strategy from all available PACTs at two VISN 12 sites to a random sample of PACTs from anywhere in VISN 12 to minimize contamination.

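### The baseline begins after measure design, so the planned contrast estimates the added effect of feedback and aids rather than the full effect of criteria and feedback named in H1

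*Protocol article*

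**What the plan says.** Two sections headed Begin measuring coordination define the baseline. Under Phase 2: "The period between completion of phase 1 and identification of point-of-care aids will serve as a baseline", with the qualifier "during this period, we will provide no feedback, only passively monitor coordination". Under Phase 3: "we will use the time period between completion of phase 1 and completion of phase 2 to passively monitor coordination at all study sites". The Phase 2 Design section confirms that baseline collection starts in phase 2, using the phase 1 measures. No earlier measurement is described. The performance period opens when leadership approves the document recommending the aids (Phase 3, Identify point-of-care aids).

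Project description and study design describes the measurement and feedback arm as two sites "which will be involved in designing the coordination measures and identifying the point-of-care aids and will receive periodic feedback on their coordination performance". The control arm is monitored passively.

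Overview of ProMES methodology says that developing the measures "teaches PACT members what effective coordination should look like" and that developing indicators and contingencies "helps clarify roles and routines (thereby improving predictability and accountability"). Develop point-of-care aid recommendations adds that the phase 1 output gives PACT members critical guidance on goals, expectations and acceptable performance.

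H1 (Objectives) compares sites that adopt measurable criteria and feedback with control sites. Phase 3 Data analysis tests it by comparing across arms the improvement from the baseline period to the performance period in a growth curve model.

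**The concern.** A baseline for H1 should precede the thing whose effect H1 names. Here H1 names two components, criteria and feedback, and the baseline precedes only the second. The intervention arm enters it after phase 1 and is still working on the aids while it runs. The control arm has had neither exposure.

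If measure development works as the article says, part of the H1 effect is already in the intervention arm's baseline level and is subtracted from the result. A small or null result could then mean that the programme does little, or that some of its benefit came early. The planned data could not tell these apart.

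**Working it through.** **1. Order of events, from the sections cited above**

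| Interval | Intervention arm | Control arm | Measured? |
|---|---|---|---|
| Before phase 1 | nothing | nothing | no |
| Phase 1 | takes part in measure design | nothing | no |
| Phase 2 (baseline) | takes part in identifying aids, no feedback | passive monitoring | yes |
| Performance period | monthly feedback, aids | passive monitoring | yes |

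**2. What the contrast recovers**

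Let m_I and m_C be the pre-design levels in the two arms, t1 and t2 the common time trend at baseline and performance, E the intervention-arm gain present by baseline, and F the further gain by the performance period.

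- Intervention change: (m_I + E + F + t2) − (m_I + E + t1) = F + t2 − t1
- Control change: (m_C + t2) − (m_C + t1) = t2 − t1
- Difference between arms: **F**
- Full effect in H1: **E + F**

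If E is positive, as the article expects, the contrast falls short of the H1 effect by E. The arm difference at baseline is (m_I − m_C) + E. It does not isolate E, because the intervention arm is two sites not described as randomly chosen, so E is mixed with site differences. A gain that arises within phase 2 drops out of a period comparison to the extent that it lifts the baseline average. Under a single slope fitted through all time points, some of it would be counted.

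**3. How wide the direct exposure is**

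- Design team: 6–10 people (Abstract, Methods/design). Arm: about 152 members in 28 PACTs (Phase 3, Participants).
- Share of members: 6/152 = 3.9% to 10/152 = 6.6%.
- If every design-team member sat in a different intervention-arm PACT: 6/28 = 21% to 10/28 = 36% of PACTs would hold one.
- Time per design-team member before baseline: 8 h (one day, an assumed length) + about 25 h + 6–8 h = 39–41 h. A further 6–8 h, and two to four meetings on the aids, fall within phase 2.
- Advisory team: one 1-h review in phase 1, plus review of the aid findings in phase 2. Its size is not given.

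**4. What this could mean for power (illustration only)**

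The plan states 80% power at δ = 1.13 and 87% at δ = 1.25, with 6 sites, 10 PACTs per site, a site intraclass correlation of 0.02 and about 12 assessments. A cluster-trial F test has noncentrality δ²·6 / {4·[0.02 + 0.98/(10r)]} on 1 and 4 degrees of freedom, where r is the reliability of the PACT-level measure. The article does not give r. With r = 1, power is 84.8% and 90.7%. With r = 0.85 it is 80.0% and 86.9%, which matches the stated pair, so I use that value.

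Let f be the average share of the total effect present by baseline. With no spread beyond design-team PACTs, f = (k/28)·g, where k is the number of PACTs holding a design-team member and g is the share of the full effect that such a PACT gains early. The documents do not give g; I assume 10% to 50%.

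- Low: (6/28) × 0.10 = 2%
- High: (10/28) × 0.50 = 18%

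| f | Power, total effect 1.13 | Power, total effect 1.44 |
|---|---|---|
| 0 | 80% | 94% |
| 2% | 79% | 93% |
| 10% | 72% | 89% |
| 18% | 64% | 83% |

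Spread through the advisory team would raise f. Specialty representatives without a PACT in the arm would lower it. The table shows sensitivity; it does not estimate the loss. The finding rests on steps 1 and 2.

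**The case against.** The strongest reply is that the window is a sound pre-feedback baseline. The article claims only that no feedback is given in it, which is true, and the Abstract describes the intervention as monthly reports and sessions. Few staff are directly exposed, and no step in phases 1 or 2 distributes the criteria to all intervention PACTs. In the section on aid recommendations, the PACT members who now have guidance can be read as the design team. This stands, and it limits the likely size. It does not answer the mismatch, because H1 covers the criteria as well as feedback, and Project description and study design counts design work as part of what the intervention arm does.

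Several stronger readings are tempting but not supported:

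- **That the trial cannot answer aim 3.** The added effect of feedback and aids remains estimable, and gains that emerge after baseline still enter the comparison. Bias toward no effect cannot by itself produce a false positive.
- **That a definite share of the effect is lost, judged by comparing the cited 1.44 with the detectable 1.13.** The documents give no such share. Nor do they say whether the meta-analysis measured change from before or after measure development.
- **That advisory members promote the whole project before baseline.** Phase 1 Participants has them championing the resulting aids, which are settled only at the end of phase 2.
- **That the baseline is shrinking.** Trial status says "The core study team is currently in phase 2 of the study and preparing for phase 3" while phase 1 is nearly complete. Overlap could shorten the window, but no length is stated, and this is a separate matter from prior exposure.

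It is also fair to say that the indicators did not exist before phase 1 and that one sample indicator is a patient survey. Replacing the baseline outright could therefore break the summed composite. The fix has to allow for that.

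**Conclusion.** The concern holds in limited form. The planned contrast estimates the increment from feedback and aids after measure design, not the full effect stated in H1. For H1 the bias, if there is one, is toward no effect.

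This rests on the article's own statements that measure development improves coordination, on the intervention arm's part in it, and on there being no measurement before phase 1. It assumes that some of that improvement exists by baseline and persists. The size cannot be derived from the documents and may be modest, given the small number of staff directly involved. The change is worth making because it alters what a null or small result would mean, and because Trial status shows phase 3 still in preparation.

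**What to change.** 1. Keep the present window, but call it a pre-feedback development period.
2. For every indicator computable from existing records, extract a fixed window that ends before the first phase 1 design meeting. Do this for every PACT in both arms, including control PACTs drawn from anywhere in the network under the revised sampling described in Trial status.
3. Fit the growth model with three periods (pre-design, development, performance) on a composite built from the same back-fillable indicators throughout. In the notation above, the arm difference in change from pre-design to development gives E, and from pre-design to performance gives E + F.
4. Keep the planned contrast on the full composite, and state that it estimates the increment from feedback and aids after measure design.

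The cost is some protocol wording and one extra data pull; Operational partners says the network provides access to related clinical data. Indicators without history, such as surveys, are left out of the pre-design composite, so it is narrower than the full one. How many can be back-filled is not known, because data sources were still being finalised. If few can be, item 4 is the minimum.

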#### Develop point-of-care aid recommendations

The final development step will involve crafting a document recommending specific point-of-care aids by which PACT members could receive prioritized point-of-care information. The prioritized list of coordination objectives and performance indicators developed in phase 1 provide PACT members with critical guidance: they know what the objectives are in coordinating care, what is expected of them, which aspects of coordination are most important, and what level of performance is considered acceptable. The team now has what it needs to identify its coordination information needs. For each objective and its respective indicators, the design team will review the performance indicators and contingency functions to answer the question, “What coordination information does each PACT member need to accomplish these objectives to the levels of performance described in these indicators and contingency functions?” The design team will be guided by the Okhuysen and Bechky model, and they will identify information needs with the goal of maximizing accountability, predictability, and common understanding. Once the list is generated, the design team can use the indicator contingencies to prioritize the information needs. To accomplish this, the design team will convene for a total of 6–8 h. Focus groups meetings will be recorded and field notes taken in order to accurately capture the design team’s recommendations.

We will hold two to four meetings with the design team to elicit the requirement characteristics of the point-of-care aids. The discussion will be guided both by Okhuysen and Bechky’s model as well as literature on best practices for feedback delivery [26, 27].

#### Leadership approval

The research team will compile the results from the multiple meetings into a single set of findings. These findings will be presented to the advisory team for their review and feedback. The design team will then refine the point-of-care aid ideas based on the advisory team’s feedback. The design team and research team together will then present the finalized point-of-care aid recommendations to leadership for approval.

## Phase 3: assess the effect of adopting the aforementioned coordination standards and point-of-care aids on PACT clinicians’ coordination behaviors

### Design and site selection

Our study will take place at four facilities within Network 12 with a high degree of alignment with PACT. Within this subset, we will select sites based on geography (rural vs. urban) and size (CBOC vs. VAMC) to ensure maximum variation; we will approach sites uninvolved in other projects from this CREATE to ensure an uncontaminated study design.

### Participants

For this phase, we will recruit members of all available PACTs at the four Network 12 study sites. Given our site selection criteria, we estimate each study arm will have an average of approximately 152 members clustered into 28 PACTs. For purposes of informed consent, we will treat all PACT members at a site as study subjects; we are aware that not all PACT members may consent to participate; however, our intervention is an intent-to-treat design, and the unit of analysis is the PACT, not the individual PACT member (our outcome of interest, coordination, is by definition a collective construct). Consequently, as long as at least the provider of a given PACT consents, we will include that PACT’s data in our analyses, taking into consideration the limitations of that PACT’s data.

Optimal design software developed by Raudenbush and colleagues [28] was used to calculate the estimated effect size for varying levels of power for a multilevel cluster randomized trial with repeated measures. With a two-tailed alpha of 0.05 and 6 sites with an average of 10 PACTs per site, an intra-class correlation coefficient for sites of 0.02 (estimated from prior VA data), and approximately 12 repeated assessments, we have 80 % power to detect a medium-to-large effect size (*δ* = 1.13) and 87 % power to detect a large effect (*δ* = 1.25). Pritchard and colleagues’ [19] meta-analysis examining the effectiveness of ProMES as improving productivity found a large overall effect size (*δ* = 1.44); accounting for moderators, effect sizes were as high as 2.21. Thus, we should be able to adequately detect improvements using the proposed number of PACTs.

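### The stated 80%/87% power was computed for six sites and 60 PACTs in a cluster randomised trial, a design the article does not describe; no power is given for the four-site layout or the amended control sampling

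*Protocol article*

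**What the plan says.** The power paragraph (Phase 3, Participants) describes a multilevel cluster randomised trial with repeated measures. Its inputs are a two-sided 5% level, "6 sites with an average of 10 PACTs per site, an intra-class correlation coefficient for sites of 0.02" and about 12 assessments. It reports 80% "power to detect a medium-to-large effect size" of 1.13 and 87% power at 1.25, cites a meta-analytic effect of 1.44, and concludes that the proposed number of PACTs is adequate.

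The design sections say something else:

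- Phase 3, Design and site selection: "Our study will take place at four facilities within Network 12 with a high degree of alignment with PACT". Phase 2, Begin measuring coordination, also speaks of four sites.
- The Abstract and the opening of the same Participants section give 28 PACTs per arm, 56 in all.
- Project description and study design has "a measurement and feedback arm (two sites from a single regional network"), which also helps design the measures, against a control arm drawn randomly from PACTs.
- Trial status says the control arm is no longer all available PACTs at two sites but "a random sample of PACTs from anywhere in VISN 12 to minimize contamination".

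Participants and Data analysis make the PACT the unit of analysis. The model has time at level 1 and arm at level 2, and names no site level.

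**The concern.** The article attaches a power figure and a statement of adequacy to a layout that it describes nowhere else. Six sites is neither four sites nor two sites plus a network-wide sample. A control arm sampled at random from PACTs is not random allocation of sites to arms.

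This is more than a miscount. The power method takes sites as clusters, so the number of sites sets the error degrees of freedom, and with so few sites power depends heavily on them. A null result would be read against 80–87% power that was never computed for this study. The opposite risk also exists: the amended design may have more power than stated, and the article would not show it.

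**Working it through.** **Inputs from the article.** Two-sided α 0.05; J = 6 sites, n = 10 PACTs per site, site ICC ρ = 0.02; δ = 1.13 and 1.25; four sites; 28 PACTs per arm; two intervention sites.

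**Assumptions.** Equal site sizes (56/4 = 14 PACTs per site), and δ in between-PACT standard deviations. For the amended design, K = 10–20 control sites.

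**Formula (site as unit of inference).** V = ρ + (1 − ρ)/n; SE² = 4V/J; λ = δ/SE; power from the noncentral t with df = J − 2.

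**1. The article's own figure.** V = 0.02 + 0.98/10 = 0.118; SE = √(4 × 0.118/6) = 0.280.
- δ = 1.13: λ = 4.03, power 84.8% (stated 80%).
- δ = 1.25: λ = 4.46, power 90.7% (stated 87%).

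The gap does not show that the stated figures are wrong, because the PACT-level and residual variances behind the repeated-measures calculation are not reported. Solving for the variance that gives 80% at 1.13 with df = 4 yields λ = 3.761, V = 0.1354 and SE = 0.300. Power at 1.25 is then 86.8%, so the stated pair is internally consistent. This check does not confirm df = 4, since any df from 4 to 58 returns 86.8–87.3%.

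**2. Four sites, df = 2** (SE² = 4V/4 = V)

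| Variance assumption | V | SE | Power at 1.13 | Power at 1.25 |
|---|---|---|---|---|
| Stated inputs: 0.02 + 0.98/14 | 0.090 | 0.300 | 52.4% | 59.3% |
| Back-solved, excess at PACT level: 0.02 + 1.154/14 | 0.1024 | 0.320 | 48.3% | 54.8% |
| Back-solved, excess at site level: 0.0374 + 0.98/14 | 0.1074 | 0.328 | 46.8% | 53.3% |
| Back-solved V unchanged, as with 10 PACTs per site | 0.1354 | 0.368 | 40.0% | 45.9% |

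Here 1.154 = (0.1354 − 0.02) × 10 and 0.0374 = 0.1354 − 0.098. With 14 PACTs per site the range at 1.13 is 47–52%; the 40% row gives no credit for the larger sites. The main driver is the critical t, which rises from 2.78 (df 4) to 4.30 (df 2), not the loss of four PACTs.

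**3. PACT as unit of inference, 28 v 28.** Design effect 1 + 13 × 0.02 = 1.26; SE² = 4 × 1.26/56 = 0.09; λ = 1.13/0.30 = 3.77; df = 54. Power is about 96% at 1.13 and 98% at 1.25. This λ equals that of the first row above, so the whole difference between 52% and 96% is degrees of freedom.

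**4. Amended design.** SE² = ρ/2 + ρ/K + 2 × 1.154/28, with ρ = 0.02.
- K = 10: 0.010 + 0.002 + 0.0824 = 0.0944, SE 0.307.
- K = 20: 0.010 + 0.001 + 0.0824 = 0.0934, SE 0.306.

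| df | Power at 1.13 |
|---|---|
| 1 (site variance not borrowed from controls) | about 23% |
| 2 | about 51% |
| K (10 to 20) | 91% to 94% |

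At ρ = 0.10 the PACT-level term becomes 2 × 1.154 × (0.90/0.98)/28 = 0.0757. SE² is then 0.1357 (K = 10) or 0.1307 (K = 20), and power with df = K is 79–84%.

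**The case against.** The mismatch cannot be denied, but much that might be built on it can be.

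- **A reader might infer that the study's true power is about one half.** The 40–52% belongs to a two-plus-two-site layout that Trial status says has changed. It also needs df = 2 and equal site sizes, although sites are chosen to vary in size, and most rows need a back-solved variance. For the amended design, pooling site variance over the control sites at the article's own ICC gives 91–94% at 1.13, above the stated 80%. This objection stands.
- **The planned analysis takes the PACT as its unit.** On that basis power is about 96–98% at 1.13–1.25. This stands as a reason not to claim low power. It does not rescue the paragraph, which justified the sample size with site clustering and a site ICC.
- **A reader might infer that the 80%/87% was miscalculated for six sites.** The documents do not show this, because the variance components are missing.
- **A reader might set the article's health-care example, scores "on average, 0.78 standard deviations higher after implementation", against the detectable 1.13 and call the study underpowered.** That example is an after-implementation change with no control arm mentioned. The article does not say what δ is standardised against, so a common metric is an assumption.
- **Calling 1.13 medium-to-large** is a matter of label and alters no result.

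**Conclusion.** The point holds as an inconsistency in the basis of the power statement. The 80%/87% refers to six sites and 60 PACTs under cluster randomisation. The article describes four sites and 56 PACTs, now amended to two intervention sites plus network-sampled controls, with no allocation of sites by chance. The adequacy conclusion is unsupported for both layouts.

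The four-site shortfall is conditional on site-level inference and unreported variances. For the current design the range of about 23% to 94% at 1.13 rests on ICC 0.02, the back-solved PACT-level variance and an assumed 10–20 control sites. A range that wide calls for a stated calculation; it does not support a claim that power is low, or that it is adequate.

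**What to change.** Replace the power paragraph with a calculation for the design being run: two intervention sites, 28 sampled control PACTs and the expected number of control sites. State the unit of inference, the degrees of freedom, the variance components and what δ is standardised against. Show results for ICC 0.02 to 0.10. Give the resulting detectable effect in place of the adequacy statement.

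Remove the description of the trial as cluster randomised. Reconcile the site counts in Phase 2 (Begin measuring coordination), Phase 3 Design and site selection, and Phase 3 Participants with Trial status. Power at 0.78 SD may be added as a sensitivity value if the metric proves comparable.

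The cost is one recomputed paragraph and a few wording changes. No added enrolment is needed, but the stated power may become less favourable.
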